### Sample size

2.4

As of the trial planning period in 2025, no randomized controlled trial data are available investigating the effects of robotic-assisted gait training on both gait dynamics and lower-limb muscle function in children with spastic CP classified as GMFCS level IV. Due to the absence of prior randomized controlled trials in children with GMFCS level IV, the effect size for this trial was conservatively estimated based on findings from systematic reviews and meta-analyses in ambulatory children with milder CP (GMFCS I–III). While this introduces some uncertainty, it represents a standard methodological approach in feasibility trials where direct data are unavailable. Reported effect sizes from these studies are consistently large, with Cohen’s d values ranging from 0.8 for gait speed (14) to 1.65 for step length (15) improvements.

Considering the intensive, device-assisted nature of the intervention and the magnitude of improvement observed in related populations, an effect size of Cohen’s d = 1.0 was deemed appropriate for the sample size estimation in this trial. Using G*Power 3.1 software to model a two-tailed independent samples *t*-test with a significance level of 0.05, power of 0.80, and equal group allocation (1:1 ratio), a total of 34 participants (17 per group) were required to detect the hypothesized between-group differences. To accommodate a potential 5% dropout rate, the final recruitment target has been adjusted to 36 participants, ensuring adequate power to detect meaningful effects while accounting for minimal attrition.

### Randomization and blinding

2.5

Participants will be randomly assigned in a 1:1 ratio to either the intervention group (robotic gait training) or the control group (usual care) using a computer-generated randomization sequence. The allocation sequence will be generated using a random number generator in R (package randomizr version 1.0.0) to ensure allocation concealment. Block randomization with a fixed block size will be employed to maintain balance between the groups throughout the recruitment period.

The assignment will be managed by a researcher not involved in participant enrollment or outcome assessment. Group allocation will be revealed to participants and caregivers following enrollment due to the nature of the intervention, which precludes participant-level blinding. This trial will follow a single-blind design, in which the statistician performing the primary and secondary analyses will remain blinded to group allocation until all data collection and preliminary data checks are complete. All outcome assessors collecting GMFCS scores, gait parameters, ultrasound muscle measures, and psychological questionnaires will remain blinded to group allocation to minimize detection bias. In the event that unintentional unblinding occurs, this will be documented, and an independent statistician—who is not otherwise involved in the trial—will be invited to conduct additional sensitivity analyses to ensure the robustness of the findings.

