### Participants

2.3

Eligible participants will be children aged between 6 and 12 years with a clinical diagnosis of spastic CP, confirmed by a licensed pediatric neurologist from the Xiangya Hospital, Central South University. Only children classified as level IV on the GMFCS will be included. These children must rely on assistive mobility devices, such as wheelchairs or posture support walkers, for activities of daily living prior to enrollment. All participants must be medically stable, able to sit upright for at least 30 min, and capable of following simple verbal or visual instructions with caregiver support.

Children classified as GMFCS level V will not be eligible for inclusion, based on pre-study consultation with the device manufacturer and experienced pediatric physical therapists, who jointly determined that the functional and cognitive demands of the robotic exoskeleton used in this study would likely exceed the safe participation threshold for this population.

Exclusion criteria include prior administration of botulinum toxin-A injections to the lower limb muscles within 6 months prior to baseline assessment; the presence of an intrathecal baclofen pump; or a history of lower limb orthopedic or neurosurgical interventions, such as tendon lengthening or selective dorsal rhizotomy, at any time prior to study participation. Additionally, children will be excluded if they present with uncontrolled epilepsy, severe cognitive impairment, or other comorbid conditions that, in the judgment of the study physician or intervention team, may interfere with safe use of the robotic device or adherence to the study protocol.

Written informed consent will be obtained from each participant’s legal guardian prior to enrollment. When appropriate, verbal or pictorial assent will also be sought from the child.

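### One fixed block size with arms disclosed lets staff who know the size deduce some allocations, and random generation is wrongly credited with concealment

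*Protocol article*

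**What the plan says.** All the allocation details are in the protocol article, section 2.5 (Randomization and blinding).

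- Scheme: "Block randomization with a fixed block size will be employed to maintain balance between the groups throughout the recruitment period". The size is not given, and no variation of size is described.
- Concealment: "The allocation sequence will be generated using a random number generator in R (package randomizr version 1.0.0) to ensure allocation concealment".
- Disclosure: "Group allocation will be revealed to participants and caregivers following enrollment due to the nature of the intervention, which precludes participant-level blinding". Only the statistician and the outcome assessors are described as blinded. Section 2.6 has therapists supervise every robot session, so they know who is in that arm.
- Safeguard: "The assignment will be managed by a researcher not involved in participant enrollment or outcome assessment".

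Two other sections matter. Section 2.3 (Participants) includes a discretionary exclusion on account of other illness, worded as follows: "in the judgment of the study physician or intervention team, may interfere with safe use of the robotic device or adherence to the study protocol". Section 2.1 places eligibility screening and baseline assessment before randomization. On numbers, section 2.4 says "the final recruitment target has been adjusted to 36 participants".

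**The concern.** There are two separate faults, and both lie in what section 2.5 states.

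First, the concealment sentence names the wrong mechanism. A random number generator makes the sequence random when it is drawn up. Whether the next assignment stays hidden from the person deciding on the next child depends on who holds the list and how each assignment is released. No detail in a fuller document could make that sentence correct.

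Second, in a 1:1 block of known size, once one arm has used up its places the rest of the block is determined. Keeping the list with an independent researcher does not prevent this, because the deduction uses past allocations rather than the list. Those allocations are visible at least to families and to the staff who run the robot. The intervention team is also named among those who judge whether a child should be excluded, so knowledge of allocations and discretion over entry may meet in the same people.

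At stake is selection at entry. Blinded assessment does not address it. The planned model includes baseline values and so can show measured differences between the arms, but not unmeasured differences in prognosis. With 36 children, a few steered enrolments could matter.

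**Working it through.** **Number of allocations.** The article's own figure reproduces. For d = 1.0, two-sided alpha 0.05 and an exact noncentral t calculation, power is 0.781 with 16 per arm and 0.807 with 17 per arm, hence 34 in total. Then 34/(1 − 0.05) = 35.8, rounded up to 36. The check below therefore uses N = 36.

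**Inputs.** 1:1 allocation and one fixed block size (section 2.5); N = 36 (section 2.4). The block size b is assumed, because none is stated. The sizes shown all divide 36.

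**Allocations known with certainty.** Let h = b/2. The expected number of forced allocations at the end of a block is 2h/(h + 1). Over 36/b blocks this gives 36/(h + 1). This applies to someone who knows b and all past allocations.

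**Best-guess success.** If the guess is always the arm with more places left, with a coin toss when level, the expected number correct per block is h + (4^h / C(2h, h) − 1)/2. Full enumeration of the blocks of 2, 4, 6 and 12 gives the same values. Pure chance is 18 of 36.

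| b | h | Certain per block | Certain of 36 | Share | Best guess, of 36 |
|---|---|---|---|---|---|
| 2 | 1 | 1.00 | 36/2 = 18.0 | 50% | 27.0 (75%) |
| 4 | 2 | 1.33 | 36/3 = 12.0 | 33% | 25.5 (71%) |
| 6 | 3 | 1.50 | 36/4 = 9.0 | 25% | 24.6 (68%) |
| 12 | 6 | 1.71 | 36/7 = 5.1 | 14% | 23.1 (64%) |
| 18 | 9 | 1.80 | 36/10 = 3.6 | 10% | 22.4 (62%) |

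**Randomly varied sizes.** This was simulated with 3,000 runs. The guesser knows the set of sizes and all past allocations, but not the size of the current block. As a check, the same code with fixed blocks of 4 returned 11.98 certain and 25.51 correct, against 12.0 and 25.5 above.

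| Sizes | Certain of 36 | Best guess, of 36 |
|---|---|---|
| 2, 4 | 3.9 (11%) | 25.9 (72%) |
| 4, 6 | 2.1 (6%) | 24.8 (69%) |
| 2, 4, 6 | 1.4 (4%) | 25.2 (70%) |

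Varying the size removes most of the certain predictions. It does not reduce better-than-chance guessing.

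**Final imbalance with sizes 2, 4 and 6.** All blocks are even, so stopping at 36 cuts the last block, if at all, after an even number of places, and the arms differ by 0 or 2. Stopping at an odd total gives 1 or 3, and 3 arises only halfway through a block of 6.

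**The case against.** A reader might infer that recruiters in this trial will foresee many allocations. The article does not support that. It says the arm is disclosed to families, not that enrolling staff see a running list, and assignment is handled outside enrolment. Section 2.1 describes several kinds of site, so one recruiter may not see the whole sequence. Staff would also need to know or infer the block size, and with a large block little becomes certain. All of this stands, and it makes the foreknowledge conditional. It does not remove the risk: the robot sessions take place at a designated training site where robot-arm membership is plain, and the stated aim of balance throughout recruitment sits more easily with small blocks than with large ones.

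Other limits also stand:

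- Leaving the block size out of a public article is not a fault, and the release mechanism may be in the full protocol.
- Section 2.1 already puts screening and baseline before randomization, so the order of events is sound.
- Tolerance of the device is not an entry criterion. It appears in section 2.6, for setting the training. The discretion in section 2.3 is real but narrower.
- Open-label would be too broad a label. The article calls the trial single-blind, with assessors and statistician blinded.
- Best-guess success of 68% to 75% with small fixed blocks should not be offered as harm that varied blocks would cure. They leave it near 70%.

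**Conclusion.** The point holds in conditional form. The concealment sentence is wrong as written, whatever the block size. The fixed block size is an avoidable weakness when families and treating staff know the arm and part of eligibility is a matter of judgement by staff who may know earlier allocations.

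The size of the weakness depends on three assumptions that the article neither confirms nor excludes: that enrolling staff know or infer the block size, that they see past allocations, and that the block is small. Under the first two, about 18, 12, 9, 5 or 4 of 36 allocations are known in advance for blocks of 2, 4, 6, 12 or 18. The documents do not show that allocation will in fact be subverted or that the sequence is unconcealed. The sample size is unaffected. The change is worth making before enrolment, but it is not a reason to doubt the design as a whole.

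**What to change.** 1. Replace the fixed block size with permuted blocks whose sizes vary at random, for example 2, 4 and 6. Do not disclose the sizes to anyone who screens, enrols, treats or assesses. Expected certain predictions fall to about 1.4 of 36. State plainly that best-guess success does not fall.
2. Delete the claim that the R generator ensures concealment. Say instead that R generates the sequence, and that concealment rests on the independent researcher releasing each assignment singly, once the eligibility screening and baseline assessment already required by section 2.1 are recorded for that child.

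The cost is a few lines of R and two sentences of text. The downside is a small possible imbalance: 0 or 2 children at exactly 36, and at most 3 if recruitment stops at another total. Section 2.2 reports no one enrolled at submission. If enrolment has since begun, apply the change to the remaining allocations and report both schemes.

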### Intervention

2.6

The intervention group will receive robotic-assisted gait training using the RoboCT Pediatric Lower Limb Rehabilitation Robot (RoboCT Limited Co., Hangzhou, China), a pediatric exoskeleton system designed for overground locomotor training. This device integrates real-time motion sensing, adaptive control algorithms, and customizable joint actuation to deliver precise and individualized gait training for children with minimal voluntary motor control. The system includes powered actuators at the hip, knee, and ankle joints, a dynamic body-weight support harness, and multi-axis load and torque sensors for continuous monitoring of movement safety. Trajectory control is achieved through programmable gait cycles, allowing therapists to adjust joint angles, step length, and walking speed according to each child’s tolerance and progression. The device employs closed-loop feedback to ensure smooth movement execution and adaptive support. Safety features include automatic shutdown in response to excessive joint torque, misalignment detection, and redundant harness support. These integrated mechanical and control features ensure that the system can safely deliver task-specific, repetitive gait training in a pediatric population.

Robotic sessions will be conducted three times per week over a period of 24 weeks, with each session lasting approximately 45 min. All sessions will be conducted at a designated training site under the supervision of certified pediatric rehabilitation therapists. Each robotic training session will follow a structured protocol comprising several core components designed to promote safe, progressive, and task-specific gait rehabilitation. Sessions will begin with a brief warm-up period, which includes passive joint mobilization and postural alignment to prepare the child for exoskeletal engagement. Following this, participants will engage in assisted overground walking guided by the device’s programmable gait cycle, which delivers coordinated joint movements to simulate a physiological walking pattern.

Throughout the session, dynamic weight-shifting mechanisms will be activated to replicate the loading and unloading phases of gait, encouraging proprioceptive stimulation and trunk engagement. The system will allow for incremental adjustment of walking speed and step length, calibrated weekly to match each child’s individual tolerance and therapeutic progression. In parallel, integrated posture correction and trunk stabilization features will ensure proper alignment and mitigate compensatory strategies during walking.

To enhance engagement and maintain motivation, each session will incorporate a gamified feedback interface that provides real-time visual cues and positive reinforcement. These interactive elements are tailored to pediatric users and are intended to promote adherence through a rewarding, game-like experience. Load-sensing and joint torque feedback systems will continuously monitor safety and fatigue levels, enabling the exoskeleton to adjust support levels as needed. All session data will be digitally recorded to monitor progress and adjust programming parameters weekly.

Participants assigned to the control group will continue their usual care as determined by their caregivers, reflecting real-world rehabilitation practices in China. Usual care may include a combination of home-based stretching, passive range-of-motion exercises, school-based physiotherapy, or conventional outpatient therapy. To enhance comparability, all components of usual care (type, frequency, and duration) will be systematically documented at baseline and monitored during monthly check-ins. Analyses will include sensitivity and subgroup comparisons according to the type and intensity of usual care received. This approach allows us to preserve ecological validity while ensuring that outcome differences are not solely attributable to a weak or poorly defined comparator condition.

No co-interventions or crossovers between groups will be permitted during the intervention phase. Any adverse events, safety concerns, or deviations from the planned robotic training sessions will be logged and reviewed by the clinical monitoring team.

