### Ethics and dissemination

2.9

This study protocol has been reviewed and approved by the Ethics Committee of Hunan Normal University (approval number: 2025–506) and will be conducted in accordance with the ethical principles outlined in the Declaration of Helsinki. The trial protocol was prospectively registered in the ClinicalTrials.gov under registration number NCT07049523, dated July 2, 2025.

The intervention poses minimal risk to participants. The robotic exoskeleton system is clinically approved for pediatric rehabilitation and is equipped with comprehensive safety mechanisms, including load-sensitive shutdowns and postural supports. All sessions will be supervised by trained rehabilitation specialists to ensure safe operation. Participants in the intervention group may experience temporary fatigue or discomfort, but serious adverse effects are not anticipated. The potential benefits include improved gait performance, joint mobility, and psychological well-being in children with GMFCS level IV CP, a group that currently lacks access to high-intensity ambulatory interventions. Participants in the control group will not be restricted from pursuing usual care.

All personal data collected during the study will be handled in strict confidence. Participants will be assigned anonymized identification codes, and any linkage to identifiable information will be securely stored and accessible only to the principal investigators. Paper forms will be stored in locked cabinets, and electronic data will be stored on encrypted, password-protected servers. Data access will be limited to authorized research personnel. Final datasets used for statistical analysis will be fully de-identified.

The results of this trial will be disseminated regardless of the direction or statistical significance of findings. Findings will be submitted for publication in peer-reviewed, open-access journals specializing in pediatric rehabilitation, neurodevelopmental disorders, or assistive technologies. In addition, study results will be presented at national and international conferences in pediatric neurology, rehabilitation medicine, and assistive robotics. A plain-language summary of key findings will be prepared and shared with participating families and local rehabilitation centers. No participant-identifying information will be included in any reports or publications.

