Certain limitations are acknowledged. The generalizability of results may be constrained to urban clinical settings with access to robotic technology and trained rehabilitation staff. In addition, while the sample size has been calculated to detect clinically meaningful changes, the trial may be underpowered for more exploratory subgroup analyses. Another limitation relates to the heterogeneity of the control group. Because “usual care” in China encompasses a wide spectrum of caregiver-directed and outpatient physiotherapy practices, comparisons with robotic gait training may appear imbalanced. However, this design choice reflects the ecological reality faced by families of children with GMFCS IV CP, where standardized rehabilitation is often unavailable. To mitigate this limitation, we will systematically document the type, frequency, and intensity of usual care and perform sensitivity analyses across subgroups, thereby ensuring transparency and interpretability of the findings. Furthermore, ankle ROM was selected as the sole joint-level outcome due to its clinical relevance and feasibility in children with GMFCS IV CP. We acknowledge that this choice does not capture potential deformities at the knee or hip. Future studies with expanded protocols should consider multi-joint assessments to provide a more comprehensive picture of musculoskeletal adaptations.

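### Subgroup and sensitivity comparisons by usual care received rest on a post-randomisation variable and cannot give the assurance attached to them; usual care at baseline should define the subgroup

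*Protocol article*

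**What the plan says.** In section 2.6 (Intervention) of the protocol article, usual care appears as the control condition: "Participants assigned to the control group will continue their usual care as determined by their caregivers". On recording, the section says that "all components of usual care (type, frequency, and duration) will be systematically documented at baseline and monitored during monthly check-ins"; this sentence names no arm. The analysis commitment follows: "Analyses will include sensitivity and subgroup comparisons according to the type and intensity of usual care received". The paragraph closes by saying that the approach keeps ecological validity while "ensuring that outcome differences are not solely attributable to a weak or poorly defined comparator condition".

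The Discussion (section 3) lists the mixed nature of the control group as a limitation. As mitigation, it says that the investigators will document usual care and "perform sensitivity analyses across subgroups, thereby ensuring transparency and interpretability of the findings".

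Four other places bear on the point:

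- Section 2.1 puts baseline assessments before randomisation for every child.
- Section 2.5 says that families learn the allocation after enrolment.
- Section 2.8 makes the primary analysis intention-to-treat, with group, time and their interaction. Its exploratory subgroups are age, sex and baseline GMFM-IS; usual care is not among them.
- On concurrent care, section 2.6 adds "No co-interventions or crossovers between groups will be permitted during the intervention phase", and section 2.9 adds "Participants in the control group will not be restricted from pursuing usual care".

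**The concern.** A subgroup analysis keeps the benefit of randomisation when the grouping factor is fixed before allocation. Care received during follow-up is not. Caregivers choose it, knowing the arm, and may seek more or less of it because of the child's severity, their own motivation, or how the child is progressing. A difference between high-care and low-care comparisons then mixes those influences with any effect of the robot.

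The protocol asks these comparisons to carry weight. They are part of its answer to the worry that a weak control condition could explain a difference between arms, and the Discussion counts on them for interpretability. If they are confounded, they can produce or hide a difference and give false reassurance.

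A related gap affects interpretation. The article does not say what usual care children in the robotic arm keep, or whether such care would count as a barred co-intervention. The result could therefore be read as robot in place of usual care or as robot added to it.

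**Working it through.** **1. The plan's own figure.** Inputs from section 2.4: d = 1.0, two-sided alpha 0.05, power 0.80, 1:1 allocation. A two-sample t-test with noncentrality d × √(n/2) gives power 0.781 at 16 per arm and 0.807 at 17 per arm, so 17 per arm, 34 in total. For 5% dropout, 34 / 0.95 = 35.8, rounded up to 36. The stated figures reproduce and are not disputed. They fix the material at hand: 18 children per arm.

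**2. Timing of the two candidate variables.**

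| Variable | Recorded | Relative to randomisation | Can depend on arm? |
|---|---|---|---|
| Usual care at baseline | Baseline (2.6) | Before (2.1) | No |
| Usual care received | Monthly check-ins (2.6) | After, allocation known (2.5) | Yes |

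The analysis sentence uses the second. If care received is split only among controls, each part is a self-selected set with no randomised counterpart. If it is logged in both arms, the high-care children in one arm need not resemble those in the other, because allocation may influence who seeks care.

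**3. Possible size of the bias.** The protocol gives no care–outcome correlation r, so r is assumed. Suppose that the robot has no effect, that care has no effect, and that r is wholly confounding. Split controls at the median of care received and compare each half with the whole robotic arm. Under bivariate normality each half departs from the control mean by

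r × √(2/π) = 0.798 r (in SD).

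- r = 0: 0
- r = 0.2: 0.798 × 0.2 = 0.16
- r = 0.3: 0.798 × 0.3 = 0.24
- r = 0.4: 0.798 × 0.4 = 0.32

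With positive r, the robotic arm looks better by this amount against the lower-care half and worse by the same amount against the higher-care half.

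**4. Check by simulation.** 50,000 replicates, 18 per arm, control halves of 9, no true effect, tests at two-sided 0.05.

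| r | Bias, lower-care half | Bias, higher-care half | Rejects, lower-care | Rejects, either half | Rejects, all children |
|---|---|---|---|---|---|
| 0 | 0.00 | 0.00 | 5.2% | 9.5% | 5.0% |
| 0.3 | +0.23 | −0.23 | 8.7% | 16.5% | 5.0% |
| 0.5 | +0.38 | −0.38 | 15.0% | 29.2% | 5.2% |

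The biases sit slightly below the formula because the split is at the median of only 18 values. The 9.5% at r = 0 comes from making two uncorrected tests; only the rise above it is due to confounding. The comparison of all randomised children stays at about 5% throughout.

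**5. What the valid alternative can show.** With a baseline factor that splits both arms, a stratum has 8 or 9 children per arm. Power at d = 1.0 is 0.46 (8 per arm) to 0.51 (9 per arm), and 80% power needs d of about 1.5 to 1.4. For the interaction, four cells of 9 give a standard error of √(4/9) = 0.67 SD, against √(2/18) = 0.33 SD for the main comparison. It is twice as large, so the test is exploratory only.

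**The case against.** The best case for the plan has several parts.

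- **The trial's randomisation is intact.** A reader might infer from the problem that randomisation is broken. The documents do not support that. The primary analysis takes all randomised children by arm, and usual care enters neither that model nor the subgroup list in section 2.8. This stands, and it limits the point to supplementary analyses.
- **Care may be logged in both arms.** A reader might infer that usual care is recorded only for controls. It is described only under the control condition, but the recording sentence names no arm. The pre-randomisation record needed for a valid subgroup may already be planned. This stands, but it does not rescue the analysis as worded, because care received is a post-randomisation variable in either case.
- **No contradiction on concurrent care.** A reader might set the bar on co-interventions in section 2.6 against the freedom given to controls in section 2.9. Usual care is the controls' assigned condition, so both sentences can hold. The abstract and section 2.1 also present the arms as alternatives. What remains is silence on background care in the robotic arm.
- **The claim is modest.** It says not *solely* attributable, refers to the whole approach of the paragraph, and sits beside an open statement of the limitation. This stands in part. *Ensuring* is still more than these analyses can deliver.
- **The size is hypothetical.** The correlation is assumed, the protocol specifies no median split, and part of any correlation could be a real effect of care. At r = 0.4 a reader might quote 0.64 SD, but that is the distance between two contrasts (2 × 0.32); either one alone is biased by 0.32 SD.
- **Detail belongs in the analysis plan.** Cut-points and models do. The choice of care received as the grouping variable, and the claim attached to it, are fixed in the article.

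**Conclusion.** The concern holds for the planned secondary comparisons. Grouping by usual care received conditions on something that unblinded families decide after randomisation, so these comparisons are open to confounding by severity, motivation and progress. They cannot secure the interpretation that section 2.6 and the Discussion assign to them.

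The size is conditional. It is about 0.16 to 0.32 SD in each single contrast, in opposite directions, if the correlation is 0.2 to 0.4, is wholly confounding, and controls are split at the median. It is nil at zero correlation. The error rate of the primary intention-to-treat comparison is untouched, although the wording of its conclusion depends on what background care the robotic arm has. Even a valid subgroup by baseline care would not turn usual care into a dose-matched comparator. The change should be made, but the trial's main result does not turn on it.

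**What to change.** 1. Define any usual-care subgroup from the type and intensity recorded at baseline, before randomisation, in both arms. Add it to the exploratory list in section 2.8 as a single group-by-baseline-care interaction, and say that power is low with 36 children.
2. Record care received on the same form in both arms at the monthly check-ins. Report it descriptively by arm, with no subgroup treatment effects by care received.
3. State what background usual care the robotic arm keeps and whether it counts as a co-intervention under section 2.6. Word the trial's conclusion for that contrast.
4. Remove or soften the *ensuring* statements in section 2.6 and the Discussion.

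The cost is small: changes of wording, and one log form used in both arms. Baseline documentation of usual care is already planned, and section 2.2 reports no enrolment when the manuscript was submitted.
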